### Recruitment {15}

Patients will be recruited via the surgical planning tool of the electronic hospital record system. The planning tool is scanned weekly by the study coordinator and a list of probably eligible patients (all scheduled transsphenoidal surgeries) is presented to the surgeon.

This is a multicenter study, recruiting patients in three centers in Belgium. Considering the estimated enrollment rate of one out of two patients, we aimed to finish recruitment within 4 years, starting end of 2018. In UZ Leuven, the estimated number of yearly inclusions is 40. AZ Sint-Jan Brugge estimates to enroll 10–15 subjects per year, and in UZ Gent, 30–40 patients are expected to enroll yearly. However, recruitment for this study has been affected by the COVID-19 crisis in multiple ways. First, EETA is not considered as emergency surgery, so these procedures were postponed during the pandemic. Second, EETA is considered a high-risk procedure for disease transmission due to perioperative aerosol formation. Third, the involvement of the third center was postponed until 2022 because of regulatory delays related to the SARS-CoV-2 pandemic. Therefore, recruitment will be extended by an additional 2 years, aiming for the finalization of recruitment in 2024.

## Assignment of interventions: allocation

### Sequence generation {16a}

The patients are randomly divided in two groups, i.e., one arm to be treated with commercially available fibrin sealants and the other arm with L-PRF. The study coordinator has generated the randomization schedule, using an online randomization tool (https://www.sealedenvelope.com) for simple randomization with two treatment groups of equal size, no blocks, and no stratification factors.

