### Intervention description {11a}

A team of neurosurgeons and otorhinolaryngologists perform the surgery according to local standards. If a patient is assigned to be treated with L-PRF, the use of commercially available fibrin sealants for sellar closure is not allowed. However, if deemed necessary by the surgeon, additional autologous (pericranium, muscle, fat grafts…) or allogenic (fascia lata) and hemostatic materials (cellulose sponges such as Spongostan® (Ethicon Biosurgery, Johnson and Johnson, New Brunswick, NJ, USA), Floseal® (Baxter, Deerfield, IL, USA), or Surgicel® (Ethicon Biosurgery, Johnson and Johnson, New Brunswick, NJ, USA)), can be used in both groups.

The L-PRF membranes are prepared during surgery. In order to ensure protocol adherence, the L-PRF preparation is performed by the study coordinator for study subjects assigned to treatment with L-PRF. In order to guarantee an optimal membrane formation, timing is of particular importance in this procedure. Therefore, the arterial line is flushed and immediately 20 mL of arterial blood is collected in a sterile syringe, transferred to two sterile 10-mL glass tubes (A-PRF®, Process for PRF, Nice, France), and instantaneously put in a centrifuge at 2700 rpm (400 g) (IntraSpin®, Intra-Lock, Boca Raton, FL, USA). During the transfer to the glass tubes and the start of the centrifugation, a second batch of 20 mL arterial blood is collected in a sterile syringe. This batch is transferred to 10-mL glass tubes as well, while the first centrifugation process is interrupted, and for ensuring a precise timing, the tubes are added into the centrifuge when decelerated. Then the centrifuge is instantly restarted at 2700 rpm for 12 min. If deemed necessary, an additional 20-mL syringe can be collected to fill two more 10-mL glass tubes and to be added to the centrifuge in a similar way.

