### Concealment mechanism {16b}

The allocation list is uploaded into the Research Data Capturing solution (RedCap) system with access restricted to study personnel. Only one subject’s allocation can be released at a time, after confirming that the patient is suitable for randomization. The site-specific study coordinator or his/her delegate enrolls the patients.

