## Assessment of interventions: blinding

### Who will be blinded? {17a}

The randomization is single-blinded, i.e., enrolled patients do not know which group they are allocated to. Blinding of surgical staff is not possible as L-PRF is clearly different from fibrin sealants. Bias of surgeons is reduced as much as possible by announcing the treatment arm only after surgical incision. Reporting bias during hospital follow-up is reduced as the paramedics at the neurosurgery hospitalization department do not have access to the randomization code. The ENT specialist performing postoperative endoscopic examinations and applying the crusting score is blinded. Researcher’s bias during follow-up visits is reduced by reblinding subject allocation after surgery. For analysis, group allocation will only be released after the statistical analysis has been performed.

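### List generation, screening, release of the arm and L-PRF preparation all fall to the study coordinator with no stated separation from enrolment, so concealment is not assured and re-blinding of that role is not credible

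*Protocol article*

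**What the plan says.** The roles are spread over several sections of the protocol article.

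- Sequence generation {16a}: "The study coordinator has generated the randomization schedule". The scheme is "simple randomization with two treatment groups of equal size, no blocks, and no stratification factors".
- Recruitment {15}: "The planning tool is scanned weekly by the study coordinator", who then gives the surgeon a list of probable candidates.
- Concealment mechanism {16b}: "The allocation list is uploaded into the Research Data Capturing solution (RedCap) system with access restricted to study personnel". It adds "Only one subject’s allocation can be released at a time, after confirming that the patient is suitable for randomization", and then "The site-specific study coordinator or his/her delegate enrolls the patients".
- Implementation {16c}: the arm is drawn in RedCap during surgery by trained personnel, a term the section itself equates with the study coordinator, and is telephoned to theatre.
- Intervention description {11a}: "the L-PRF preparation is performed by the study coordinator for study subjects assigned to treatment with L-PRF".
- Who will be blinded? {17a}: patients and the ENT specialist who does the postoperative endoscopy are blinded, and ward paramedics have no access to the code. For researchers the section says that "bias during follow-up visits is reduced by reblinding subject allocation after surgery".

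**The concern.** Concealment means that nobody who can influence whether a patient enters the trial knows the next assignment. Here the role that wrote the list also finds candidates and draws the arm, and may enrol. If one person does these things, the next arm can be known when a patient is approached or when suitability is confirmed, and patients can be steered, deliberately or not. Analysis cannot repair that afterwards, and Methods for additional analyses {20b} plans no adjusted analyses.

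The second issue is the re-blinding statement. Hiding a field in the database does not remove what a person already knows. Someone who drew the arm or prepared the membranes for a patient still knows that patient's treatment at the follow-up visits, where questionnaires are completed and open-ended harms questions are asked.

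**Working it through.** The point contains no figure of its own, so the check is a comparison of stated roles.

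| Task | Who, as stated | Section |
|---|---|---|
| Generates the list | study coordinator | {16a} |
| Scans for candidates | study coordinator | {15} |
| Sends the information brochure | study coordinator | {26a} |
| Takes consent, before surgery | trained study staff | {26a} |
| Enrols | site-specific coordinator or delegate | {16b} |
| Confirms suitability | not named | {16b} |
| Draws the arm, during surgery | study coordinator | {16c} |
| Prepares L-PRF | study coordinator | {11a} |
| Postoperative endoscopy | ENT specialist, blinded | {17a} |
| Transfers data to RedCap | research assistant | {18a} |

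**Step 1: can past assignments reveal the next one?** No. The sequence is simple, unblocked and unstratified. The only route to foreknowledge is having seen the list.

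**Step 2: who may have seen it?** Its author, the study coordinator. Possibly others too: access is limited to study personnel, and {16c} uses nearly the same term for the study coordinator. No section says that the author or the recruiters are locked out.

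**Step 3: does single release after confirmed suitability close the gap?** It does for a person who has never seen the list. It does not for its author, who can know the next slot before it is released.

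**Step 4: does the author also screen or enrol?** {15} and {16a} use the same term for screening and generation. For enrolment, {16b} uses a site-specific term across three centres. The overlap is stated for screening at role level. For enrolment it is possible but not stated.

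**Step 5: whom can re-blinding cover?** It can cover staff who took no part in drawing the arm or preparing the L-PRF for that patient. It cannot cover those who did, and under {16c} and {11a} that is the study coordinator.

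**Sample size, for completeness.** Inputs from Sample size {14}: success 0.943 (control) and 0.95 (L-PRF), margin 0.07, one-sided alpha 0.05, power 80%.

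n per arm = (1.645 + 0.842)² × (0.943 × 0.057 + 0.95 × 0.05) / (0.95 − 0.943 + 0.07)² = 6.18 × 0.10125 / 0.005929 ≈ 105.6, so 106 per arm and 212 in total, as stated. Nothing in this point changes that number.

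**The case against.** The strongest reply is that the article nowhere shows the generator and the recruiters to be one person. The site-specific wording in {16b} suggests several coordinators, and for those who did not write the list the single-release rule is a real safeguard. The access sentence may describe the RedCap system rather than open viewing of the list, and detailed user rights are normally left to the full protocol. The opportunity to select is also limited: the list shown to the surgeon covers all scheduled transsphenoidal operations, the neurosurgeon introduces the study, consent precedes surgery, and the arm is drawn only in theatre. If all centres draw from one list, as the absence of stratification suggests, the next slot is hard to match to a given patient at the time of approach.

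Most of this stands, and it limits the point. A reader might infer that allocation is not concealed from recruiters anywhere; the text does not support that. What remains is that none of these safeguards acts on the author of the list. With one common list, the author would still know the next slot when suitability is confirmed during surgery.

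On blinding, a reader might infer that follow-up assessment as a whole is unblinded. That is not supported either. The ENT endoscopist is blinded without relying on re-blinding, questionnaires are completed on paper by blinded patients, a research assistant transfers the data, and no section says that the coordinator assesses outcomes. The criticism reaches only those who drew the arm or prepared the product.

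A reader might also want to express the bias as a share of the 7-point margin. That requires an assumed number of patients steered between arms, and the article offers none. The expected enrolment of one in two candidates does not supply it, because no reasons for non-enrolment are given.

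**Conclusion.** The point holds in a limited form. As written, the protocol gives generation, screening, release and L-PRF preparation to one role and does not separate them from enrolment. Concealment fails wherever the author of the list also screens or enrols, and is not assured elsewhere. Re-blinding is not credible for anyone involved in that patient's randomisation or L-PRF preparation.

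The size of any bias cannot be derived from the article. The conclusion rests on reading the study coordinator as the same role throughout, and on the absence of any stated lock-out of the list's author. If different people in fact hold these tasks, and the author has no contact with recruitment, the concealment part reduces to a need to say so. The re-blinding part stays. The change is worth making because it is cheap and because selection bias, once present, cannot be corrected.

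**What to change.** 1. For all allocations not yet released, have a RedCap administrator or a statistician with no recruitment role generate and load a new list, and block access to it for coordinators and anyone who screens or enrols. State both in {16a} and {16b}.
2. In {17a}, limit the re-blinding statement to staff who took no part in that patient's randomisation or L-PRF preparation.
3. Assign follow-up questionnaires, harms questions and outcome entry to existing staff who meet that condition, for example the research assistant named in {18a}.

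Trial status describes recruitment as ongoing, so unreleased allocations could still be protected; the article does not say how many remain.

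Cost: a short amendment, filed with the ethics committee as {25} requires, a few hours of data management, and some reallocation of tasks among existing staff at three sites.

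I would not add an analysis comparing results before and after the change. At the assumed rates the whole trial expects about 106 × 0.05 + 106 × 0.057 = 5.3 + 6.0 ≈ 11 failures, and the part after the change would hold too few to be informative.

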### Concealment mechanism {16b}

The allocation list is uploaded into the Research Data Capturing solution (RedCap) system with access restricted to study personnel. Only one subject’s allocation can be released at a time, after confirming that the patient is suitable for randomization. The site-specific study coordinator or his/her delegate enrolls the patients.

### Implementation {16c}

Randomization is done during surgery using the Randomize-tool in RedCap by trained study personnel, i.e., the study coordinator. The arm to which the patient is allocated is communicated by telephone to the operation theatre staff.

## Assessment of interventions: blinding

### Who will be blinded? {17a}

The randomization is single-blinded, i.e., enrolled patients do not know which group they are allocated to. Blinding of surgical staff is not possible as L-PRF is clearly different from fibrin sealants. Bias of surgeons is reduced as much as possible by announcing the treatment arm only after surgical incision. Reporting bias during hospital follow-up is reduced as the paramedics at the neurosurgery hospitalization department do not have access to the randomization code. The ENT specialist performing postoperative endoscopic examinations and applying the crusting score is blinded. Researcher’s bias during follow-up visits is reduced by reblinding subject allocation after surgery. For analysis, group allocation will only be released after the statistical analysis has been performed.

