Leukocyte- and platelet-rich fibrin (L-PRF) is a biologically active material that is derived from the patient’s own blood [6]. L-PRF can be prepared in solid form as membranes or as plugs, or as a liquid. The main advantage of L-PRF is that it is completely autologous, thereby minimizing the risk of immunological reactions. Additionally, L-PRF is non-invasive, inexpensive, and can be prepared in a 20-min time span. Solid L-PRF is obtained by centrifuging a small sample of blood for 12 min at 400 g in glass or silica-coated tubes (Fig. 1), during which the coagulation cascade is initiated, and different blood components are separated. The resulting blood clot is the actual L-PRF, situated right above the red blood cell layer. It is in fact a fibrin matrix that contains a high concentration of platelets, leukocytes, and growth factors. These growth factors would promote tissue healing and reduce inflammation, which makes L-PRF an attractive option to use in a variety of surgical procedures. Analogously, liquid L-PRF glue can be prepared in plastic-coated tubes. Because of the hydrophobic surface and shorter centrifugation time (3 min), the product maintains its native fibrinogen and only coagulates in contact with other tissues [7].

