After the centrifugation process, the presence of a dense clot right above the red blood cell layer in the tubes is verified. If these are not present, the tubes are put aside for 10 min and inspected again. The tubes are opened and presented to the scrub nurse for removing the clot with sterile forceps. The clot is placed in an Xpression Box® (Intra-Lock, Boca Raton, FL, USA) and gently compressed by placing the compression plate and the lid on top. After 5 min, the membranes are ready for surgical application by placing them on the dural defect. If necessary, the membranes can remain in the Xpression box® for up to 3 h until application. An instruction video of the L-PRF preparation process is available at http://doi.org/10.5281/ZENODO.8095217 [13].

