### Criteria for discontinuing or modifying interventions {11b}

After allocation to the experimental or control arm, several circumstances—specified as perioperative exclusion criteria- can still lead to excluding the patient from the study. A patient allocated to the control arm may be excluded in case of a clear indication for a hypersensitivity reaction to commercially available fibrin sealants. Patients allocated to L-PRF treatment may be excluded if the L-PRF preparation process fails or if the product is considered of insufficient quality. In case the surgeon identifies other intraoperative findings that may constrain the conduct of the study procedure the subject can be excluded as well, to ensure optimal patient care in that situation. For example, when the damage to the dura is exceptional, the surgeon may opt for a multilayer reconstruction using multiple grafts, commercially available sealants, and autologous materials. Furthermore, study participants can withdraw from the study at any moment, implying that all subsequent study procedures and data collection are discontinued.

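### Announcing the arm after incision sets only a lower bound: leak, defect and intended reconstruction need not be recorded first, so grafting and exclusions can be decided with the arm known

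*Protocol article*

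**What the plan says.** Section {17a} accepts that the operating team will know the arm: "Blinding of surgical staff is not possible as L-PRF is clearly different from fibrin sealants". Its safeguard for surgeons is the timing of disclosure: "Bias of surgeons is reduced as much as possible by announcing the treatment arm only after surgical incision".

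The other sections do not narrow that timing. Section {16c}: "Randomization is done during surgery using the Randomize-tool in RedCap by trained study personnel, i.e., the study coordinator". Section {16b} adds one condition: "Only one subject’s allocation can be released at a time, after confirming that the patient is suitable for randomization". It does not say that suitability must be judged after the defect has been seen, or that any operative finding must be on record.

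Two sections leave decisions to the surgeon:
- On co-interventions, {11a} says "However, if deemed necessary by the surgeon, additional autologous (pericranium, muscle, fat grafts" and goes on to allogenic fascia lata and hemostatic materials, all permitted in both groups.
- On exclusions after allocation, {11b} says "In case the surgeon identifies other intraoperative findings that may constrain the conduct of the study procedure the subject can be excluded as well". Its example is exceptional dural damage.

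Section {20c} plans an intention-to-treat analysis of everyone randomized, beside per-protocol and as-treated analyses.

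**The concern.** Two decisions that can move the leak rate, how much extra material to add and whether the patient stays in the trial, depend on what the surgeon sees well after incision. A surgeon who knows the arm and trusts one product less may reinforce more in that arm, or may withdraw a difficult case from it. Neither needs bad intent.

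In a non-inferiority trial the risky direction is compensation in the experimental arm. It pulls the two success rates together and so favours the claim. Few events are expected, so a handful of altered outcomes matters. Little downstream would correct it: allocation is simple, without blocks or strata ({16a}), no adjusted analyses are intended ({20b}), and intraoperative data come from reports filed by the operating neurosurgeon and ENT surgeon ({18a}).

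**Working it through.** **1. What the timing rules permit**

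| Question | Section | Answer |
|---|---|---|
| Earliest announcement | {17a} | Incision |
| Stage of randomization | {16c}, Randomization under {13} | During surgery, no step named |
| Condition for release | {16b} | Suitability confirmed |
| Leak, defect or graft plan recorded before release | none | Not required |
| Exclusion on operative findings after allocation | {11b} | Allowed |
| Extra grafts | {11a} | Surgeon's judgement, both arms |

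The fifth row is decisive. If exceptional dural damage can lead to exclusion after allocation, the plan itself foresees cases in which the arm is allocated before the defect is judged.

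**2. The plan's own sample size**

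Inputs from {14}: control success 94.3%, L-PRF success 95%, margin 0.07, one-sided alpha 0.05, power 80%.

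n per arm = (1.645 + 0.842)² × (0.943×0.057 + 0.95×0.05) / (0.07 + 0.007)² = 105.6, rounded up to 106, so 212 in total. This agrees with the protocol. At 110 per arm the expected failures are 110 × 0.057 = 6.3 and 110 × 0.05 = 5.5, about 6 per arm.

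**3. Sensitivity (the bias sizes are assumed)**

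Put true L-PRF success, under equal grafting, on the margin: 94.3% − 7% = 87.3%. With 110 per arm and a normal approximation,

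P(claim) = Φ[(0.07 − (pC − pT))/SE − 1.645], SE = √(pC(1−pC)/nC + pT(1−pT)/nT).

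Without bias this is 5%.

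*Extra grafting averts a fraction f of L-PRF failures:* pT = 1 − 0.127(1 − f).

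| f | pT | Difference | P(claim) |
|---|---|---|---|
| 0 | 87.30% | −7.00 points | 5.0% |
| 10% | 88.57% | −5.73 points | 9.6% |
| 20% | 89.84% | −4.46 points | 17.2% |
| 30% | 91.11% | −3.19 points | 28.9% |

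For f = 20%: SE = √((0.0538 + 0.0913)/110) = 0.0363; (0.07 − 0.0446)/0.0363 − 1.645 = −0.945; Φ = 0.172.

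*k would-be failures leave the L-PRF arm and are not followed:* pT = 1 − (13.97 − k)/(110 − k). P(claim) is 7.6%, 11.3% and 16.4% for k = 1, 2 and 3.

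**4. What intention-to-treat repairs**

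If excluded patients are followed and counted, the exclusion route closes. But {11b} speaks of excluding them from the study, while {20c} counts everyone randomized. The two must be reconciled. The grafting route stays open either way, because intention-to-treat keeps each patient's outcome as altered by the extra graft. The per-protocol and as-treated analyses do not remove it either, since additional grafts are allowed in both arms.

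**5. Is later release workable?**

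Section {6a} says that L-PRF "can be prepared in a 20-min time span" and that this can run in parallel with surgery. The steps in {11a} are 12 minutes of centrifugation and 5 of compression (17), with 10 more if no clot is seen (27), plus blood collection: roughly 20 to 30 minutes. Once made, "the membranes can remain in the Xpression box® for up to 3 h until application".

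**The case against.** A reader might infer that the arm is announced straight after incision, before resection, and that every later decision is made with the arm known. The text does not say so. It gives a lower bound and a suitability check, and a site may in practice release late. The supportable claim is that these decisions *can* be made with the arm known.

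It can also be said that the exact surgical step is detail which a condensed article leaves to the full protocol. That would answer a complaint about mere silence. Here the article states a rule, claims that it reduces bias as far as possible, and describes exclusions on operative findings after allocation. A site that follows the rule as written permits the bias.

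Other objections stand in part:
- The same extra materials are allowed in both arms, and defects, grafts and materials are recorded. An imbalance in grafting would therefore be visible. It could not be attributed, because no record made before release shows what was intended.
- Intention-to-treat helps with exclusions, within the limit shown above.
- The direction is not established. Extra grafting could occur in either arm.
- Harm to an adjusted analysis by leak status is not a valid complaint: {20b} rules out adjusted analyses and does not list intra-operative leak among its subsets.
- Preparing L-PRF early without the surgeons' knowledge is doubtful. Blood is drawn from the patient's arterial line for L-PRF cases, and the scrub nurse handles the clots.
- Recruitment began in November 2018 and was to end in 2024, so a change reaches only later patients.

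**Conclusion.** The point holds in limited form. Incision is too early an anchor to support the claim that surgeon bias is reduced as much as possible, because a later and better-documented release point is available and not required. Discretionary grafting and exclusions can follow knowledge of the arm, and the planned analyses cannot undo arm-dependent grafting.

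The documents do not show that bias has occurred, in which direction, or how large it is. The rise from 5% to about 10% to 29% assumes that true L-PRF success lies on the margin, that extra grafting in that arm alone averts 10% to 30% of its failures, and that the test uses the one-sided 0.05 level of the sample-size section. The sample size itself is correct and needs no change. The amendment is worth making, but the point does not invalidate the trial.

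**What to change.** For patients still to be randomized:

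1. Make release in RedCap conditional on a short e-CRF entry, made once the defect can be assessed: suitability confirmed in light of operative findings, intra-operative leak (yes/no), defect size and intended reconstruction. Telephone the arm only after that. The surgeon stays free to depart from the recorded plan.
2. Report departures from the recorded plan, and exclusions after release, by arm.
3. Reconcile {11b} with {20c}, so that patients excluded after allocation are still followed and counted in the intention-to-treat analysis.
4. If the present timing is kept, delete the words *as much as possible* from {17a}.

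Cost: an amendment, one form and, in L-PRF cases, a possible wait of roughly 20 to 30 minutes, partly absorbed by work done before closure. Hidden earlier preparation should not be relied on to avoid the wait. Data from patients already enrolled are unaffected, so the report should state from which date the new procedure applied.
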